#### Secondary outcomes

The secondary outcome measures comparing standard dressings to NPWT dressings in this trial are:

Number of recruited patients within the internal pilot will be assessed;Number of all wound complications (composite) in each arm will be collected;Number of SSIs in each arm will be assessed: any SSI meeting the CDC criteria will be documented and described as superficial or deep;Number of wound dehiscence rates in each arm within 6 months of index surgery will be assessed: any wound dehiscence will be documented and described as superficial or deep;Number of days to discharge for each arm will be assessed: the length of time the patient is in hospital from date of surgery to both the date of discharge and the date that the patient is deemed medically fit for discharge will be recorded;Number of reoperations within 6 months of index surgery in each arm will be assessed: any reoperations undertaken will be recorded;Number of readmissions to hospital within 6 months of index surgery in each arm will be assessed: all readmissions to hospital related to the surgical procedure will be recorded;Impact on quality of life: the EuroQoL EQ-5D-5L questionnaire is a validated measure of health-related quality of life. It comprises a five-dimension health status classification system and a separate visual analogue scale;Differences in wound-related quality of life in the 6 months following major amputation will be captured using the Wound-QoL questionnaire;Economic impact: the financial impact of patients’ out-of-pocket expenses will be recorded using the validated CoPaQ questionnaire. Patient self-reported information on service use has been shown to be accurate^11^. Healthcare resource use will be recorded for the economic analysis. Unit cost data will be obtained from national databases where available but where not available the unit cost will be estimated in consultation with the hospital finance department;Resource use and cost-effectiveness data, including number of NPWT devices utilized and troubleshooting with NPWT devices.

## Trial population

### Inclusion criteria

Adult patients, aged 18 and over, with capacity to consent undergoing lower extremity amputation, including BKA, through-knee amputation, and AKA, for any indication, suitable for primary closure of the surgical incision using either interrupted or continuous sutures.

### Exclusion criteria

Women who are pregnant and/or breastfeeding;Amputations performed without primary skin closure, including guillotine amputations, amputations deliberately left open for drainage purposes, and amputations with soft tissues defects at the stump;Clinically absent femoral pulse.

### Recruitment and informed consent

#### Informed consent of the inpatient

Patients will be screened from clinic and operating lists in trial centres. All patients listed for a major amputation will be assessed for eligibility. Screening logs will be maintained at each site to record the number of patients assessed for eligibility and the reasons for any exclusions. Those patients who decide they do not wish to participate or withdraw from the study will be given the opportunity to discuss with the research team the reasoning behind the decision to not take part.

The process of obtaining informed consent will be conducted in compliance with the principles of good clinical practice and requirements of the approving research ethics committee. Patients will be approached for consent before they have the operation. Consent to enter the trial will be sought from each subject only after a full written and verbal explanation has been given and, insofar as is possible, time allowed for consideration. Patients will be provided the opportunity to ask questions and discuss the study with the research team. Patients will be given an information leaflet (*supplemental data 1*). As a reasonable percentage of major amputations are performed as urgent or emergent procedures, in these circumstances the available time for consideration will be truncated. The consent process will be conducted by the trial investigators in all cases. All original signed consent forms will be kept in the investigator study-specific site file. There will be three copies of each consent form: one for the patient’s medical record, one for the patient, and one for the study team.

#### Informed consent of the outpatient

The minority of patients undergoing major amputation may come to a shared decision in the outpatient setting and then return at a separate date for elective admission. Eligible patients will be given an information sheet at their outpatient visit and the trial will be explained to them by a team member. Written informed consent will be obtained immediately before the procedure by an investigator.

### Randomization

Following the consent process, eligible patients will be enrolled in the study through the online randomization system at the time of surgery in the operating theatre. Randomization will be on a one-to-one basis using a computer randomization program, with balanced allocation of patients across the two treatment groups, stratified by trial centre. All monitoring operating theatres can provide immediate internet access permitting the use of a secure 24-hour web-based randomization system to generate treatment allocation during surgery. Final eligibility will be confirmed by the treating surgeon at the end of the operative procedure before the wound dressing is applied, as a small subset of patients may be deemed clinically inappropriate for wound closure. A unique trial number will be assigned to each individual at the time of randomization. Patients will be randomized to one of two groups. There will be no sham intervention.

Group 1: single-use NPWT device applied to the closed skin incision after amputation.

Group 2: standard dry dressing applied to the closed skin incision after amputation.

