#### Standard dressing

Standard dressing for an amputation wound comprises a non-adhesive layer applied directly to the wound, covered by a sealed dressing, supplemented with protective padding. Such standard dressings do not use negative pressure. The precise details of the materials used will be at the discretion of the treating surgeon as per their routine practice but the details of each dressing applied in the trial will be noted. The duration that each dry dressing is left *in situ* varies between surgeons, though the majority will leave the first dressing for a minimum of 48 hours and a maximum of 5 days. For the purpose of this trial, the type and duration of control dressing will be recorded, including the postoperative day the dressing was first removed.

Of note, it is some surgeons’ usual practice to use a drain in the amputation stump delivered out through a separate incision to protect against haematoma formation; the drain is usually ready for removal at 48–72 hours after surgery. There is a lack of high-quality evidence supporting drain use after major amputation; however, it a widespread practice. Achieving a durable seal for NPWT around a drain can be technically challenging, and a seal may be lost once the drain is removed; extra care should be taken to maintain a seal once the drain is removed. For the purpose of this study, surgeons should not alter their regular practice regarding drain use. The presence or absence of a wound drain will be recorded in the procedural data, allowing for potential subanalysis of the impact of drain use on outcomes.

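### The protocol does not require final eligibility and wound closure to be settled before the allocation is released, so concealment up to those decisions is not assured

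*Protocol article*

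**What the plan says.** The Randomization section of the protocol article makes three statements about timing.

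- Enrolment: "eligible patients will be enrolled in the study through the online randomization system at the time of surgery in the operating theatre".
- Allocation: theatres have internet access "permitting the use of a secure 24-hour web-based randomization system to generate treatment allocation during surgery".
- Final check: "Final eligibility will be confirmed by the treating surgeon at the end of the operative procedure before the wound dressing is applied". The reason given is that "a small subset of patients may be deemed clinically inappropriate for wound closure".

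The same section says there is no sham. Suitability for primary closure is an inclusion criterion, and the Exclusion criteria rule out "Amputations performed without primary skin closure, including guillotine amputations, amputations deliberately left open for drainage purposes".

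Three other places bear on the point.

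- **Standard dressing** warns that "Achieving a durable seal for NPWT around a drain can be technically challenging". It also tells surgeons to keep to their usual drain practice, has drain use recorded, and foresees a possible subanalysis by drain.
- **Withdrawals during follow-up** lets the principal investigator withdraw a participant who meets an exclusion criterion. Data up to withdrawal are kept and none are collected afterwards. **Protocol violations** separately allows exclusion after randomisation for inability to follow trial procedures.
- **Crossovers** and **Statistical analysis** both commit to intention to treat.

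**The concern.** Concealment has to last until the decision to enter a patient is final. Here the last entry decision is a judgement by the treating surgeon about whether the stump can be closed. If the arm is already known, that judgement can be influenced by it, even without intent. A randomised patient whose stump is left open meets an exclusion criterion and may be withdrawn, so the two arms could lose different patients. The stated intention-to-treat analysis cannot recover outcomes that are no longer collected.

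Drain placement raises a lesser version of the same issue. The protocol itself gives an arm-specific reason to prefer no drain under negative pressure wound therapy (NPWT). If drain use followed a known arm, a subanalysis by drain would condition on a variable affected by randomisation.

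**Working it through.** **Step 1: order of events.** The two timing statements, side by side:

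| Event | When | Tied to |
|---|---|---|
| Allocation generated | During surgery | No particular point in the operation |
| Final eligibility confirmed | End of the operation | Before the dressing |

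The end of the operation, before dressing, is still within surgery. Two sequences therefore fit the text:

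- (a) allocate, close, check eligibility, dress;
- (b) close, check eligibility, allocate, dress.

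No sentence rules out (a) and none mandates it. Sites in a multicentre trial could follow different sequences and all comply.

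**Step 2: consequence under (a).** With no sham, the surgeon knows the arm once it is released. A decision not to close then makes the patient ineligible after randomisation, and the withdrawal rule allows removal. Under (b) such a patient is never randomised and the problem does not arise.

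**Step 3: the plan's own figure.** The Sample size section assumes 25% against 15%, 90% power and a 5% level; tests are two-sided. The unpooled normal formula gives

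n = (1.960 + 1.282)² × (0.25×0.75 + 0.15×0.85) / 0.10² = 10.507 × 0.315 / 0.01 ≈ 331 per arm,

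which matches the plan (the pooled-variance formula gives 335). Adding 10%: 331 × 1.10 = 364.1, taken as 364, and 2 × 364 = 728, as stated. The order of allocation and eligibility does not enter this calculation.

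**Step 4: illustration of size.** The only information on wounds unsuitable for closure is that they are a small subset. Everything below is assumed: a fraction f of one arm is lost after allocation, those patients have complication risk r, and the other arm loses nobody. An arm with true rate p then shows

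p_obs = (p − f·r) / (1 − f).

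| Arm losing patients | f = 0.03, r = 0.4 | f = 0.05, r = 0.6 |
|---|---|---|
| Standard dressing, p = 0.25 | 0.238/0.97 = 24.5% (−0.5 points) | 0.220/0.95 = 23.2% (−1.8 points) |
| NPWT, p = 0.15 | 0.138/0.97 = 14.2% (−0.8 points) | 0.120/0.95 = 12.6% (−2.4 points) |

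Losses from the standard arm would shrink the planned 10-point difference to 9.5–8.2 points. Losses from the NPWT arm would widen it to 10.8–12.4 points. The direction depends on which arm loses patients, and the documents do not say.

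**The case against.** The strongest reply is that the protocol never says allocation comes first, and several cues favour the safe sequence. It is eligible patients who enter the system. The sentences on trial number and group follow the one on final eligibility. Both arms are defined on a closed incision, and immediate internet access in theatre suits a late request. A central web system also means nobody knows the arm until it is requested. This stands to the extent that a reader might infer that the protocol places allocation before the eligibility check, and the text does not support that as fact. It does not remove the gap, because early release is nowhere barred.

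On drains, a reader might infer that drain use becomes a consequence of allocation. The protocol instructs surgeons not to change their practice, so that is only a possibility. The instruction is still not concealment. The subanalysis is described only as potential and is never called a baseline comparison.

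It can also be said that intention to treat is promised and that data up to withdrawal are kept. That is true, but a patient withdrawn at the end of surgery has no 30-day outcome to keep.

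Finally, this is a condensed article and a fuller protocol may fix the moment of release. That is a fair reason to call this an ambiguity rather than a proven fault. However, the article sets out the sequence itself and leaves the decisive step open.

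**Conclusion.** The point holds as a gap in the stated procedure. The protocol does not require final eligibility, closure and drain placement to be complete before the allocation is released, and its withdrawal rule allows a patient left unclosed to be removed after randomisation. Concealment and the intention-to-treat set are therefore not protected by the text as written.

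The documents do not show that concealment is actually broken, and they do not support a bias estimate. A reader might take the 0.5–1.8 points for the standard arm as a measured effect. The arithmetic is correct, but the figures rest wholly on an assumed 3–5% loss, an assumed 40–60% risk, and all loss falling in one arm. Both size and direction are unknown. Any such bias would be systematic, so a larger sample would not reduce it and the analysis could not reliably undo it.

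**What to change.** Reword the Randomization section to set one order:

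1. The surgeon completes skin closure and any drain according to usual practice.
2. The surgeon records final eligibility in the web system.
3. Only then does the system release the allocation, and the dressing is applied.

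State that patients whose wound is not closed are logged as screened and not randomised. State also that every randomised patient stays in the intention-to-treat set, and bring the withdrawal wording on exclusion criteria into line with this.

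The cost is a sentence or two, one mandatory field in a system already available in theatre, and a short wait before dressing. The sample size does not change. The change belongs before further patients are randomised, since it cannot be made good at analysis.

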### Baseline patient data

Patients will all have a full medical history taken and clinical examination as part of their standard care. Furthermore, a EQ-5D-5L quality of life questionnaire will be completed. The following baseline clinical and demographic data will be recorded:

Sex;Height;Weight;Year of birth;Smoking status;Diabetes;Peripheral arterial disease (Ankle Brachial Pressure Index < 0.6);Previous revascularization ipsilateral leg;Surgical speciality performing amputation;Rockwood Clinical Frailty Score (> 60 years old only).

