## Background

Major lower extremity amputations are frequently performed for unreconstructable peripheral arterial disease and progressive diabetic foot complications^1,2^. As the population ages and the prevalence of diabetes increases, rates of diabetic-related major amputations are projected to increase despite advancing revascularization techniques. In both the UK and Ireland, rates of major amputation are significantly higher in the diabetic population^3,4^. In the United States, approximately 185 000 major amputations are performed annually, and the number of patients living with limb loss is projected to double from 1.5 million to 3.6 million by 2050^5^. Up to one-third of patients experience perioperative wound complications after major amputation^6–10^. Conversion from below-knee amputation (BKA) to above-knee amputation (AKA) is estimated to occur in 12–34% of limbs, with wound infection causative in a significant number of cases^8^. The 30-day readmission rate after a lower extremity amputation ranges from 29 to 46%^9,11^. Prolonged inpatient stays, multiple procedures, costly comorbidities, and high rates of readmissions lead to patients with peripheral arterial disease accumulating hospital costs six times those of general inpatients^12^. Similarly, the healthcare costs and resource utilization of diabetic foot care in England is greater than the combined cost of breast, prostate, and lung cancers^13^.

Many factors influence the risk of wound complications^14–18^. Notably, the presence of proximal occlusive arterial disease is a major influence on stump healing. Patient factors such as smoking, diabetes, obesity, malnutrition, and chronic kidney disease are non-modifiable, particularly in the emergency setting. However, surgical factors may be altered in an effort to reduce the risk of wound complications. One variable amenable to alteration is what dressing is applied to the closed incision upon procedure completion. The type of dressing may influence factors such as bacterial access to the wound, the development of collections of blood or fluid within the wound bed, or discharging onto the wound edges. Collectively, these wound factors increase the risk of wound infection. Therefore, dressings that reduce these factors have the potential to reduce wound breakdown, thereby reducing the burden for patients and healthcare systems.

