## Statistical considerations

### Statistical analysis

Once randomization and intervention is complete, patient outcomes will be assessed using an intention-to-treat analysis. All losses to follow-up at any time point will be recorded and reported. A blinded biomedical statistician will conduct all analyses independently of the data collection team. Statistical analysis will be conducted using SPSS^TM^ Version 29 (IBM Corp, Aramonk, New York, United States). Baseline data will be summarized to check comparability between treatment arms. The main analysis will investigate differences in the primary outcome measure, the proportion of patients with any wound complication at 30 days after major amputation.

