Use of randomization by stratification should ensure balance in the recruiting centre in both treatment groups. Whereas clustering effects are not expected to be important for this study, in reality the data may be hierarchical, with patients naturally clustered into groups by recruiting centre. This will be accounted for by generalizing the conventional linear (fixed-effects) regression approach to a mixed-effects logistic regression analysis. This model will be used to assess differences in wound complication rates between the study intervention groups, with results presented as odds ratios with associated 95% confidence intervals. The mixed-effects model will include a random effect to account for any heterogeneity in response due to the recruitment centre and fixed effects to adjust for vascular status. An identically structured and formulated mixed-effects linear regression model will be used to assess the effects of the interventions on secondary outcomes and EQ-5D-5L (at 1, 3, and 6 months) that, for the purposes of analysis, will be assumed to be approximately normally distributed. Other dichotomous outcome variables, such as complications related to the trial interventions, will be analysed in the same manner as the primary outcome. Temporal patterns of any complications will be presented graphically, and, if appropriate, a time-to-event analysis (Kaplan–Meier survival analysis) will be used to assess the overall risk and risk within individual classes of complications. All reported tests will be two-sided and considered to provide evidence for a significant difference if *P*-values are less than 0.05 (5% significance level. Results from this trial will also be compared with results from other trials and reported in accordance with CONSORT guidelines. Whereas there are a multiplicity of secondary outcomes, considering CONSORT guidelines and regulatory body preferences, the authors do not plan to adjust for type 1 errors due to the high risk of a corresponding increase in type 2 errors^22^.

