### Sample size

The data on the impact of prophylactic NPWT on wound complication following major amputation are limited. Retrospective cohort studies^6–10^ of wound complications with standard therapy after amputation reportedly range from 10 to 34%. In a recent meta-analysis^21^ of NPWT for major amputations, the pooled proportion of composite wound complications for patients using NPWT was 16%. For planning purposes, and based on the previously published range, it has been assumed that 25% of participants randomized to standard dressings will develop a wound complication. To investigate an absolute risk reduction of 10% with the use of NPWT (that is, a wound complication rate of 15%), with 90% power at the 5% significance level, a minimum of 331 patients will be required in each arm. To allow for losses to follow-up and withdrawals, 10% will be added to each arm. Therefore, the total projected sample size for the full trial is 728 patients.

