Furthermore, this randomized feasibility trial aims to evaluate the cost-effectiveness, tolerability, and impact on patients’ quality of life of NPWT. In their Cochrane review of NPWT across surgical specialities, Normal *et al*.^19^ noted that pain and health-related quality of life were not reported by most of the included RCTs. The absence of robust cost-effectiveness data to support the routine use of NPWT is also of concern. NPWT is considerably more expensive than traditional dressings (approximately £120–145 versus £4 for a standard dressing), and cost-effectiveness studies^19^ produced differing results across varied settings with no high-grade evidence of cost efficacy. While comparing the cost of the device against the potential saved cost of avoided complications, the cost of devices used improperly without achieving the desired effect must also be considered. As such, it is felt that the feasibility outcome of monitoring the durability of these devices in the ward setting on amputation stumps will provide helpful information. Potential pitfalls in real-world practice using NPWT devices include premature removal by unfamiliar healthcare staff or devices left unsealed where the colloid interface soaks with exudate and macerates the wound edges. The anticipated strength of this trial is its pragmatic design and adequate power to account for the multiple confounding factors associated with poor wound healing in this high-risk cohort.

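### The primary model could also adjust for diabetes, smoking and age, whose baseline data are already recorded: a small gain in test power, not the repair of an error

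*Protocol article*

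**What the plan says.** All references are to the protocol article.

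- **Statistical analysis.** The primary outcome is "the proportion of patients with any wound complication at 30 days after major amputation". It is analysed by mixed-effects logistic regression with a random effect for recruiting centre and "fixed effects to adjust for vascular status". Results are odds ratios with 95% confidence intervals, and tests are two-sided at 5%.
- **Background.** Proximal arterial disease is singled out as a major influence on stump healing. The text then turns to patient-level factors: "Patient factors such as smoking, diabetes, obesity, malnutrition, and chronic kidney disease are non-modifiable".
- **Baseline patient data.** The recorded fields include "Smoking status;Diabetes;Peripheral arterial disease", together with year of birth, height, weight and previous revascularization of the same leg.
- **Randomization.** Allocation is 1:1, stratified by centre only.
- **Sample size.** The calculation starts from the statement that "it has been assumed that 25% of participants randomized to standard dressings will develop a wound complication" and takes 15% for NPWT: "with 90% power at the 5% significance level, a minimum of 331 patients will be required in each arm". Adding 10% per arm gives 728 in total.
- **Discussion.** The authors expect "adequate power to account for the multiple confounding factors associated with poor wound healing in this high-risk cohort".

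**The concern.** The protocol names diabetes and smoking as risk factors for the primary outcome and records both before treatment. It neither stratifies on them nor puts them in the primary model. Adjusting for baseline variables that predict a binary outcome usually raises the power of the treatment test. Here the data are already being collected, so the plan may leave some power unused. At stake is how much power that is, and whether the omission harms the planned analysis in any other way.

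**Working it through.** **1. The plan's own figure.** Inputs from Sample size and Statistical analysis: 25% v 15%, two-sided 5%, 90% power, 1:1 allocation. With unpooled variance:

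n per arm = (1.960 + 1.282)² × (0.25 × 0.75 + 0.15 × 0.85) / 0.10² = 330.98, so 331.

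331 × 1.1 = 364.1, and 364 × 2 = 728. Both figures reproduce. The calculation is an unadjusted comparison of two proportions, so it relies on no covariate. The planned effect as a marginal odds ratio is (0.15/0.85) / (0.25/0.75) = 0.53, a log odds ratio of about −0.64. Expected events are 331 × (0.25 + 0.15) ≈ 132.

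**2. What adding diabetes and smoking would change.** The document gives no prevalences or odds ratios for these factors. The following are therefore assumptions: diabetes 60%, smoking 40%, vascular disease 60%; vascular odds ratio 1.5; covariates independent; no centre effect. Marginal rates were held at 25% and 15%. For each scenario, 4,000 trials of 662 evaluable patients (2 × 331) were simulated. Each trial was analysed by logistic regression twice: with treatment and vascular status (standing in for the stated model), and with diabetes and smoking added.

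| Assumed OR, diabetes / smoking | Power, stated | Power, with both | SE of log OR | Mean log OR | Equivalent sample-size gain |
|---|---|---|---|---|---|
| 1.0 / 1.0 | 89.7% | 89.4% | 0.2016 → 0.2022 | −0.6424 → −0.6443 | 0.0% |
| 1.3 / 1.3 | 89.1% | 89.4% | 0.2016 → 0.2028 | −0.6425 → −0.6482 | 0.6% |
| 1.5 / 1.5 | 90.1% | 90.6% | 0.2016 → 0.2036 | −0.6454 → −0.6553 | 1.1% |
| 2 / 1.5 | 90.1% | 90.7% | 0.2013 → 0.2044 | −0.6429 → −0.6590 | 2.0% |
| 2 / 2 | 90.2% | 91.4% | 0.2014 → 0.2058 | −0.6459 → −0.6715 | 3.5% |
| 3 / 2 | 89.8% | 91.3% | 0.2014 → 0.2081 | −0.6424 → −0.6819 | 5.6% |
| 3 / 3 | 89.9% | 92.1% | 0.2012 → 0.2111 | −0.6425 → −0.7019 | 8.4% |

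The last column is the ratio of (mean log OR / SE)² between the two models, minus 1. At 3/3 this is (0.7019/0.2111)² / (0.6425/0.2012)² = 1.084. The Monte Carlo standard error of each power figure is √(0.9 × 0.1 / 4000) ≈ 0.5 point, so the gains at odds ratios of 1.3 to 1.5 are no larger than that noise.

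**3. Reading the table.** Under the stated model, power is about 89% to 90% throughout, so the target is met without the extra terms. The gain is about 0 to 1 point for odds ratios up to 2 and about 2 points at 3/3. The standard error goes up, not down. Power rises only because the conditional log odds ratio moves away from zero faster than its standard error grows. At 2/2, |estimate|/SE goes from 0.6459/0.2014 = 3.21 to 0.6715/0.2058 = 3.26. The half-width of the 95% interval on the log scale goes from 1.96 × 0.2014 = 0.395 to 1.96 × 0.2058 = 0.403.

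**4. Chance imbalance.** For a factor with an assumed 60% prevalence, the 95% range of the between-arm difference is ±1.96 × √(2 × 0.6 × 0.4 / 331) = ±7.5 points. With an assumed odds ratio of 2, that shifts the log odds ratio by about 0.075 × ln 2 ≈ 0.05. The standard error is about 0.20.

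**The case against.** The strongest reply is that nothing in the plan is wrong. The model contains the only stratification factor, centre, and the one factor the Background calls a major influence, arterial disease. Randomization balances diabetes and smoking in expectation, and the test's error rate already covers chance imbalance. The sample size reproduces and its power holds. All of this stands, and it is why the point is minor.

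A reader might infer more in four ways that the document does not support:

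- **Lost precision.** The protocol reports an odds ratio, and adjustment slightly widens the interval for its logarithm.
- **Bias towards 1.** The less adjusted odds ratio lies nearer 1 because odds ratios are non-collapsible. It is valid for its own, less conditional, effect. The planned 25% v 15% contrast is itself marginal, so further adjustment moves the reported odds ratio away from 0.53.
- **A contradiction with the Discussion.** The remark about power and confounding factors is general prose and promises no set of covariates.
- **An undefined vascular status.** Its exact definition is commonly left to the analysis plan, which is not shown.

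It can also be said that any covariate list is partly a matter of choice. The Background's list of patient factors does not include age, and obesity is named there but is not in the proposal below. That is fair. A further caution also stands: under complete-case fitting, missing covariate values could cancel a gain worth only 0 to 3.5% of the sample size.

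What remains is that two named, recorded risk factors are unused in a model that could take them at no cost to patients.

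**Conclusion.** The point holds as an optional improvement of minor weight. The stated primary model is valid, unbiased under randomization and adequately powered against the protocol's own target. Adding diabetes and smoking would raise power by about 0 to 1 percentage point for odds ratios up to 2 and by about 2 points if both are 3. It would not narrow the interval for the log odds ratio.

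These sizes rest on assumed prevalences and odds ratios, independent covariates and no centre effect. If diabetes or smoking is correlated with vascular status, part of their information is already in the model and the gain would be expected to be smaller. Age was not simulated, so the figures claim nothing for it.

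**What to change.** In Statistical analysis, before unblinding, state the fixed effects of the primary model as treatment, vascular status, diabetes, smoking status and age (from year of birth), with the random centre effect as planned. Report the currently stated model, with centre and vascular status only, as a sensitivity analysis. Say that the primary odds ratio is conditional on these covariates, so that readers do not set it directly against the marginal 0.53 behind the sample size. State how missing baseline values are handled, so that no patient drops out of the primary analysis because of them.

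Do not add amputation level unless its capture is confirmed; it is not among the listed baseline fields.

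The cost is wording only: no new data, no change to the 728, and a few extra model terms against about 132 expected events.
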